### Study endpoints

FVEP stimulation, data recording, and storage will all be performed using the Medtronic NimEclipse neuromonitoring system. The same experienced neuroelectrophysiologist will monitor intraoperative FVEPs for all procedures.

The primary endpoint of this study is the N75-P100 amplitude at 60 min after the induction of anesthesia, which is defined as the mean N75-P100 amplitude on O1, O2, and Oz leads in both eyes.

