The secondary endpoints are as follows:N75-P100 amplitude decline rate compared to baseline measured under TIVA, calculated by the formula $$\frac{\left[N75-P100\left(TIVA\right)-N75-P100\left(HD\right)\right]}{\left[N75-P100\left(TIVA\right)\right]}\times100\%$$ or $$\frac{\left[N75-P100\left(TIVA\right)-N75-P100\left(LD\right)\right]}{\left[N75-P100\left(TIVA\right)\right]}\times100\%$$. N75-P100 (TIVA) will be measured 30 min after anesthesia induction under TIVA in both groups. N75-P100 (HD) or N75-P100 (LD) will be measured 60 min after anesthesia induction in HD or LD group.P100-N145 amplitude decline rate compared to baseline measured under TIVA, calculated by the formula $$\frac{\left[P100-N145\left(TIVA\right)-P100-N145\left(HD\right)\right]}{\left[P100-N145\left(TIVA\right)\right]}\times100\%$$ or $$\frac{\left[P100-N145\left(TIVA\right)-P100-N145\left(LD\right)\right]}{\left[P100-N145\left(TIVA\right)\right]}\times100\%$$. P100-N145 (TIVA) will be measured 30 min after anesthesia induction under TIVA in both groups. P100-N145 (HD) or P100-N145 (LD) will be measured 60 min after anesthesia induction in HD or LD group.Rate of prolongation of P100 latency compared to TIVA baseline measurements, calculated by the formula $$\frac{\left[P100\left(HD\right)-P100\left(TIVA\right)\right]}{\left[P100\left(TIVA\right)\right]}\times100\%$$ or $$\frac{\left[P100\left(LD\right)-P100\left(TIVA\right)\right]}{\left[P100\left(TIVA\right)\right]}\times100\%$$. P100 (TIVA) will be measured 30 min after anesthesia induction under TIVA in both groups. P100 (HD) or P100 (LD) will be measured 60 min after anesthesia induction in HD or LD group.The success rate of FVEP monitoring is defined as the ratio of the number of eyes with a satisfactory waveform to the number of all monitored eyes.FVEP stacking satisfaction will be assessed by electrophysiologists. A satisfactory waveform that could be evoked no more than three times will be considered satisfactory.Intraoperative anesthetic and vasoactive drug dosage, including anesthetics (i.e., sufentanil, remifentanil, propofol, rocuronium) and vasoactive agents (i.e., atropine, ephedrine, noradrenaline, phenylephrine, urapidil)Recovery quality:Respiratory recovery time is defined as the time from the cessation of anesthesia to the patient’s spontaneous breathing.Eye-opening time is the time from anesthesia cessation to when the patient can be called to open their eyes.Extubation time is defined as the time from the cessation of anesthesia to the removal of the patient’s tracheal catheter.Post-extubation agitation score. Ratings will be performed immediately after awakening and 15, 30, and 60 min after awakening: 1 point—restful sleep; 2 points—awake and calm; 3 points—irritability or irritability or crying; 4 points—difficulty to comfort or uncontrollable crying; 5 points—unable to be quiet or confused or delirium.Post-extubation sedation score. Ramsay sedation scale will be administered to the patients immediately after awakening and at 15, 30, and 60 min after awakening: 1 point—awake but anxious and restless; 2 points—cooperation, orientation, quiet; 3 points—drowsiness and response to commands; 4 points—drowsiness, rapid response to tapping eyebrow or loud auditory stimuli; 5 points—lethargy, slow response to tapping eyebrow or loud auditory stimuli; 6 points—drowsiness, no response at all. Scores 2–4 indicate satisfactory sedation and 5 to 6 excessive sedation.

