### Sample size calculation

We used PASS 15 to calculate the sample size for this study. According to the pre-experiment results, at 60 min after induction of anesthesia, the amplitudes of the LD group and HD group were 3.43 ± 0.78 μV and 2.37 ± 0.80 μV, respectively. According to the results of other studies, the superiority margin was defined as 20% of the N75-P100 amplitude in the HD group [6]. According to *α* = 0.025 and *β* = 0.2, a sample size of 63 cases can provide a superiority margin of 20% higher amplitude in the LD group than in the HD group. We conservatively set the dropout rate at 10% on the basis of actual 1.7% in our previous study, the sample size should be a total of 70 persons will be enrolled, and 35 patients in each group.

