### Statistical analysis

All data analyses will be performed on both a per-protocol (PP) and intention-to-treat (ITT) basis. The intent-to-treat population will include all subjects randomized to receive HD or LD anesthesia maintenance, and the completed FVEP data will be collected. The per-protocol population will include all subjects in the ITT population not identified as protocol violators (i.e., change in the anesthesia strategy after the trial initiates). These protocol violations will be shown in a listing. Subjects who do not obtain available FVEP data or abandon the study for various reasons will be considered to have failed HD/LD and will be excluded from any form of analysis. For the missing data, the last observation and the worst-case imputation scenarios will be used as the main interpolation method.

The statistical analysis will be performed by an independent statistician using SPSS V.25.0 (Somers, NY, USA). Histograms and the Shapiro‒Wilk test will be used to assess the normality of the data distribution. For the statistical description, the continuous variables will be presented as the mean (standard deviation, SD) for normally distributed data or median (interquartile range, IQR) for skewed distributions. Categorical variables will be reported as counts and percentages, and the relative risk with its 95% confidence interval (CI) will be calculated. The absolute standard deviation (ASD) will be determined to identify any imbalance in baseline characteristics.

The primary outcome (N75-P100 amplitude of FVEPs recorded 1 h after induction) will be analyzed using a superiority test. According to the results of other studies, the superiority margin was defined as 20% of the N75-P100 amplitude in the HD group [6].For secondary outcomes, *χ*^2^ tests or Fisher’s exact tests will be performed for categorical variables including N75-P100 amplitude decline rate, P100-N145 amplitude decline rate, rate of prolongation of P100 latency, success rate of FVEP monitoring, FVEP stacking satisfaction, adverse events related to FVEP monitoring, and recovery quality. Anaesthetic and vasoactive drug agent consumption will be analyzed using independent samples *t*-tests for normally distributed variables and Wilcoxon sum tests for variables with skewed distributions. The study will terminate after all the data for the last patient are collected.

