A 1-sided *P* value of 0.025 will be considered statistically significant for the primary outcome. If the confidence interval for mean differences of N75-P100 amplitude between LD and HD groups lied above the lower limit of *δ* with *P* < 0.025, we defined LD group will be superior to HD group. While all *P* values will be 2-sided with a significant level of 0.05 for the comparisons of N75-P100 amplitude decline rate, P100-N145 amplitude decline rate, rate of prolongation of P100 latency, success rate of FVEP monitoring, FVEP stacking satisfaction, anaesthetic and vasoactive drug agent consumption, and adverse events related to FVEP monitoring or recovery quality between the group LD and HD.

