Neuromonitoring is usually performed under TIVA, which is also true for FVEPs. However, TIVA may not be suitable for lengthy surgeries needing motor-evoked potential monitoring with strict restriction for muscle relaxant supplements, especially during long-term spine surgery or neurosurgery. Intravenous-inhalation combined anesthesia has the advantage of synergistically acting on GABA and NMDA receptors that reduce the dosage of anesthetics and weaken the suppression of FVEPs. However, its impact on intraoperative FVEP monitoring has not been conclusive, and to the best of our knowledge, there are only a few relevant studies. In 2017, the Uribe study first proposed that compared with TIVA, desflurane-propofol balanced anesthesia greatly reduces the amplitude of FVEPs and prolongs their latency [16]. However, this study has many limitations. First, a combination of drugs was used for the balanced anesthesia group, including dexmedetomidine, remifentanil, and propofol. The doses of each drug were not clear. The synergistic effect of the combination of multiple drugs may aggravate the effects on FVEPs. Second, the range of BIS values was not strictly limited. Third, the small sample size (*n* = 19) may produce false positive or negative results. In 2021, we conducted a noninferiority study, which showed that the effect of sevoflurane 0.5 MAC combined with propofol and remifentanil-balanced anesthesia on the P100-N145 amplitude was not inferior to that of the TIVA group [17]. In our previous study, two groups of patients were controlled within the same BIS range combined with ERG monitoring, and the success rate of FVEP monitoring was 100%. Thus, our conclusion suggests a new anesthesia approach of sevoflurane-propofol balanced anesthesia maintenance for FVEPs besides TIVA. Yet, the effect of inhalation at different concentrations on FVEPs remains unclear. Desflurane has the advantage of high anesthesia recovery quality [22]. We hypothesize that desflurane-propofol balanced anesthesia can benefit the monitoring of FVEPs during spinal surgery compared with desflurane alone.

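### FVEP monitoring success is counted per eye but tested as if the two eyes of one randomised patient were independent, so its P value and confidence interval are not valid in general

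*Protocol article*

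**What the plan says.** All references are to the protocol article.

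- **Unit.** Study endpoints defines success as "the ratio of the number of eyes with a satisfactory waveform to the number of all monitored eyes". Numerator and denominator are both eyes.
- **Test.** Statistical analysis states that chi-square "tests or Fisher’s exact tests will be performed for categorical variables including N75-P100 amplitude decline rate" and goes on to list "success rate of FVEP monitoring, FVEP stacking satisfaction, adverse events related to FVEP monitoring, and recovery quality". The same section plans a relative risk with 95% confidence interval for categorical variables.
- **Level.** For the secondary outcomes, success rate among them, P "values will be 2-sided with a significant level of 0.05 for the comparisons of" the two groups.
- **Randomised unit.** Randomization and blinding allocates patients 1:1. Sample size calculation gives "a total of 70 persons will be enrolled, and 35 patients in each group".
- **Eyes per patient.** The primary endpoint is "the mean N75-P100 amplitude on O1, O2, and Oz leads in both eyes", so both eyes are recorded, and for that endpoint they are reduced to one value per patient.
- **Failed recordings.** Remedy keeps patients whose FVEPs fail to record in the study. Statistical analysis says that subjects without available FVEP data "will be excluded from any form of analysis".

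The article mentions neither within-patient correlation nor a patient-level version of the success endpoint.

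**The concern.** Chi-square and Fisher's exact tests assume that each counted unit is an independent observation. Here up to 140 eyes come from 70 randomised patients. The two eyes of a patient share the allocation, the anaesthetic, its depth, the blood pressure, the temperature and the occipital electrodes. Remedy and Discussion name several of these patient-level factors as things to check when recording fails, or as influences on FVEPs. Some causes of failure are specific to one eye, such as light delivery, so the correlation need not be 1, but zero is hard to believe.

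With positive correlation, 70 eyes per arm carry less information than 70 independent observations. The P value is then too small and the relative-risk interval too narrow. At stake is a possible false claim that one regimen allows FVEP monitoring more often than the other.

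This is not a detail left to an unseen analysis plan: the article states both the unit and the test, and they do not fit together.

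**Working it through.** **Inputs from the document.** 35 patients per arm (63/0.9 = 70 enrolled), 2 eyes each, hence 70 eyes per arm; two-sided 0.05; chi-square or Fisher. The plan gives no power or error rate for this endpoint, so there is no figure of its own to reproduce.

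**Assumptions.** The ICC and the common true success rate p are not given, so both are varied. "Mixed" in the table means chi-square without continuity correction, replaced by Fisher when an expected count is below 5.

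**Step 1, large-sample approximation.** For pairs the design effect is 1 + ICC. The true error of a nominal 5% chi-square test is 2 × [1 − Φ(1.96/√(1 + ICC))], and the interval is too narrow by a factor √(1 + ICC).

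| ICC | Design effect | Effective eyes per arm (70/design effect) | True error | Interval factor |
|---|---|---|---|---|
| 0.3 | 1.3 | 53.8 | 0.086 | 1.14 |
| 0.5 | 1.5 | 46.7 | 0.110 | 1.22 |
| 0.8 | 1.8 | 38.9 | 0.144 | 1.34 |

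**Step 2, exact enumeration under equal success rates.** For each patient, P(both eyes succeed) = p² + ICC·p(1 − p), P(exactly one succeeds) = 2p(1 − p)(1 − ICC), and the remainder is P(neither). For example, p = 0.9 and ICC = 0.5 give 0.855, 0.090 and 0.055. The distribution of successful eyes per arm is the sum over 35 patients, and the rejection probability is summed over all pairs of totals.

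| Success rate | Mixed, ICC 0.3 / 0.5 / 0.8 | Fisher alone, ICC 0.3 / 0.5 / 0.8 |
|---|---|---|
| 80% | 0.087 / 0.112 / 0.148 | 0.059 / 0.079 / 0.110 |
| 90% | 0.084 / 0.107 / 0.144 | 0.050 / 0.068 / 0.098 |
| 95% | 0.044 / 0.060 / 0.093 | 0.030 / 0.043 / 0.069 |
| 98% | 0.006 / 0.010 / 0.020 | 0.006 / 0.010 / 0.019 |

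The error falls at high success because failures become scarce. The expected number of failing eyes per arm is 70 × 0.10 = 7 at 90%, 70 × 0.05 = 3.5 at 95% and 70 × 0.02 = 1.4 at 98%, so Fisher takes over and is very conservative. Even at ICC 1 the mixed rule gives 0.036 at 98% and 0.008 at 99%. If chi-square were used at 98% regardless of expected counts, the error would be 0.047 / 0.065 / 0.105.

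With 31 patients per arm (close to the 63 evaluable) the mixed results are similar: 0.083 / 0.107 / 0.143 at 80% and 0.079 / 0.102 / 0.138 at 90%.

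**Step 3, effect of the exclusion rule.** Suppose patients with both eyes failed are removed, and let d be the per-eye failure rate among those left. Then P(both succeed) = 1 − 2d, the covariance is (1 − 2d) − (1 − d)² = −d², and dividing by d(1 − d) gives ICC = −d/(1 − d). At an assumed d = 0.1 the ICC is −0.11, the design effect 0.89 and the approximate error 2 × [1 − Φ(1.96/√0.89)] ≈ 0.038. The test would then be conservative.

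**Step 4, after correction.** With one outcome per patient and 35 per arm, Fisher's test has a true error of at most 0.028 over patient-level success rates of 70% to 98%. The mixed rule gives 0.051, 0.046, 0.019 and 0.003 at 70%, 80%, 90% and 95%.

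**The case against.** The strongest reply is that the problem may have no practical effect here. The only success rate in the article comes from the group's earlier sevoflurane study, where "the success rate of FVEP monitoring was 100"%. Near that value there would be almost no failures, Fisher would apply and the error would stay under 5%. Fisher is also one of the two named tests and inflates less. Read literally, the exclusion of subjects without FVEP data could even turn the correlation negative. Finally, this is one of many secondary outcomes, and the article treats amplitude as the main measure of FVEP.

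Much of this stands as a limit on size. A reader might infer that the false-positive rate is inflated two- to three-fold. The document does not support that as a general statement. It needs the chi-square test, success of about 90% or lower and an ICC of roughly 0.45 to 0.85, and neither the success rate nor the ICC is given.

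It does not remove the mismatch. The earlier study compared sevoflurane at 0.5 MAC plus propofol with TIVA. The HD arm here receives a different agent at 0.7–1.0 MAC without propofol during maintenance, and the Background says anaesthetics can make FVEP extraction fail. A 100% rate therefore cannot be carried over, and a test should not depend on the event being too rare to matter. The exclusion rule cannot be relied on either: it conflicts with Remedy, and it is unclear whether an unsatisfactory waveform still counts as available data. It would also discard the very failures this endpoint is meant to count.

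**Conclusion.** The point holds as a mismatch between the stated unit and the stated test on a secondary endpoint: the P value and relative-risk interval for per-eye success are not valid in general.

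With 35 patients per arm and an assumed ICC of 0.3 to 0.8, the nominal 5% test (mixed rule) has a true error of about 8–15% at 80–90% success and 4–9% at 95%. It stays below 5% at 98% or more. Fisher alone gives about 5–11% at 80–90%. If patients with both eyes failed are dropped, the test could be conservative instead. Size, and under that reading direction, therefore rest on quantities the document does not give, and no single inflation factor should be quoted.

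The primary endpoint is averaged over both eyes within each patient, so it and the sample size are unaffected.

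**What to change.** 1. Keep the per-eye success rate as the descriptive measure, so the defined endpoint does not change.
2. Compare groups with a method that respects the patient as the randomised unit: a permutation test that permutes patients with both their eyes, or GEE with patient-clustered robust standard errors if failures are not too few. Replace the ordinary relative-risk interval with one based on patient-clustered variance.
3. Add a patient-level Fisher's exact test (both eyes satisfactory, yes or no) as a supporting analysis. It should not replace the endpoint, because it answers a slightly different question.
4. Reconcile Remedy with Statistical analysis. For this endpoint, count patients with failed recordings as failures, in line with Remedy and with a denominator of all monitored eyes.
5. Apply the same approach to FVEP stacking satisfaction if it is scored per eye.

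The cost is a change of analysis wording, minor extra analysis work and usually a somewhat wider interval. No new data and no more patients are needed.

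### The ordered, four-times-rated agitation score falls under chi-square/Fisher tests, which ignore its order, and neither it nor the Ramsay score has a stated per-patient comparison

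*Protocol article*

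**What the plan says.** Protocol article, Study endpoints, lists two clinician-rated scores under recovery quality.

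- **Agitation** runs from 1 (restful sleep) up to "5 points—unable to be quiet or confused or delirium". On timing: "Ratings will be performed immediately after awakening and 15, 30, and 60 min after awakening".
- **Ramsay sedation** runs from 1 (awake, anxious and restless) up to "6 points—drowsiness, no response at all". On timing: "Ramsay sedation scale will be administered to the patients immediately after awakening and at 15, 30, and 60 min after awakening". The section adds cut-offs for this scale only: "Scores 2–4 indicate satisfactory sedation and 5 to 6 excessive sedation". Score 1 belongs to neither group.

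The Statistical analysis section then says that chi-square or Fisher's "exact tests will be performed for categorical variables including N75-P100 amplitude decline rate, P100-N145 amplitude decline rate", and the same list ends with "FVEP stacking satisfaction, adverse events related to FVEP monitoring, and recovery quality". Independent-samples t-tests and Wilcoxon tests are named only for anaesthetic and vasoactive drug consumption. The section's last paragraph tests recovery quality two-sided at 0.05. It names no time point, per-patient summary or repeated-measures method for either score.

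**The concern.** The agitation score is categorical, but its categories are ordered. A chi-square or Fisher test on the five levels would give the same P value if the labels were shuffled, so it spends its degrees of freedom on patterns of no interest. It also needs one value per patient, and the plan collects four. The stated test cannot use them together, and pooling all ratings in one table would break the independence it assumes.

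Fast, good-quality recovery is a reason the article gives for using desflurane (Background and Discussion), and the groups differ in desflurane concentration. A null result from a weak test could be read as equal recovery. If each time point were tested, one significant result out of four could be over-read.

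This is separate from another problem in the same sentence, which also places recovery times and percentage changes under chi-square/Fisher. Moving those continuous outcomes to t or Wilcoxon tests would leave the two scores where they are.

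**Working it through.** The article gives no power or error rate for these scores, so there is no stated figure to reproduce.

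**Inputs from the article.** 35 patients per group (Sample size calculation); five ordered agitation levels and four ratings (Study endpoints); two-sided 0.05 (Statistical analysis).

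**Assumed inputs.** Agitation distribution in one group 15/45/25/10/5%; a proportional-odds shift with odds ratio 2.5; within-patient correlation 0.3 to 0.7.

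**Step 1: distribution in the shifted group.** The cumulative odds of a score at or below each level are divided by 2.5.

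| Score at or below | Cumulative p | Odds | Odds/2.5 | Shifted p |
|---|---|---|---|---|
| 1 | 0.15 | 0.176 | 0.071 | 0.066 |
| 2 | 0.60 | 1.500 | 0.600 | 0.375 |
| 3 | 0.85 | 5.667 | 2.267 | 0.694 |
| 4 | 0.95 | 19.00 | 7.600 | 0.884 |

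Differencing gives about 6.6/30.9/31.9/19.0/11.6%.

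**Step 2: power at one time point, by simulation.** Chi-square about 32%; Wilcoxon rank-sum about 54%.

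**Step 3: dependence on the assumptions.** With a second assumed distribution (15/50/20/10/5%):

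| Odds ratio | Chi-square | Rank test |
|---|---|---|
| 1 (no difference) | 4% | 5% |
| 2 | 17% | 34% |
| 3 | 45% | 69% |
| 4 | 68% | 87% |

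The loss at odds ratios 2 to 4 is 17 to 24 percentage points (34 − 17 = 17; 69 − 45 = 24; 87 − 68 = 19). The first row shows that the type I error of a single chi-square test is not raised.

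**Step 4: combining the four ratings.** One rank test on the patient's mean rating has power of about 85%, 76% and 67–68% at within-patient correlation 0.3, 0.5 and 0.7, if the shift is the same at all four times. Its type I error is about 5%.

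**Step 5: if every time point were tested.** For independent tests, 1 − 0.95^4 = 18.5% per scale. Simulation with correlated ratings gives at least one P<0.05 in about 15% of null trials per scale, roughly three times the nominal 5%.

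**Step 6: does the same remedy suit Ramsay?** By the article's own labels, 1 is undesirable, 2–4 satisfactory and 5–6 excessive. A patient rated 1 and later 5 averages (1 + 5)/2 = 3, which falls in the satisfactory range. Take assumed distributions of 5/40/30/20/4/1% against 22/25/13/12/20/8%. The share within 2–4 is 40 + 30 + 20 = 90% against 25 + 13 + 12 = 50%. Chi-square on the full scale detects this contrast with power of about 85%, the rank test with only 8–9%. A rank or mean comparison can therefore miss a difference that lies at both ends.

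**The case against.** **Number of tests.** A reader might infer that the plan commits to eight separate tests, four per scale, and so to an inflated error rate. The article does not say so. It names recovery quality once, and the choice of time point or summary may stand in an analysis plan that is not shown. This objection stands: the 15% figure is conditional on testing each rating.

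**Ramsay cut-offs.** The stated grouping offers a categorical reading for which chi-square/Fisher is suitable. This also stands, although the article does not say that the grouping is what will be tested, and score 1 has no group. Multiplicity is also smaller on a binary outcome: four Fisher tests at assumed event rates of 10% or 20% give at least one P<0.05 in about 5% or 9–10% of null trials.

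**Power loss.** A reader might conclude that chi-square is the weaker choice for both scores. That depends on a one-directional shift, which is reasonable for agitation but not assured for Ramsay, as step 6 shows. The gain from averaging also assumes a constant effect over the hour; averaging would dilute an early difference that fades.

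**What remains.** The article is not silent on the test for agitation. It names one that ignores order, gives agitation no cut-off that would make the test suitable, and uses Wilcoxon elsewhere in the same section. An analysis plan that followed the article would carry the weakness over.

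**Conclusion.** The point holds for the agitation score. The stated test discards the order and cannot use the repeated ratings; under the assumed distribution and odds ratio 2.5 this costs about 22 percentage points of power at one time point (54 − 32). The distribution, odds ratio and correlations are assumptions. The loss is of similar size under a second assumed distribution, provided the effect runs in one direction. The figures use all 35 enrolled per group; with the planned 10% dropout both powers would be somewhat lower.

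For Ramsay the test family can stay. What is missing is the single per-patient outcome to which it applies, including where score 1 goes.

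The documents support neither a claim that eight tests are planned nor a claim that chi-square inflates type I error at a single time point. This is a minor to moderate point on secondary outcomes; the N75-P100 comparison is unaffected.

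**What to change.** In the Statistical analysis section:

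1. **Agitation.** Take it off the chi-square/Fisher list and name one order-respecting comparison: either a Wilcoxon rank-sum test on one prespecified per-patient summary (the mean or the worst of the four ratings), or a proportional-odds model with time and a patient random effect, reported as a common odds ratio with 95% CI. If an early, fading difference is expected, weigh that before choosing the mean.
2. **Ramsay.** Do not use the mean score. Keep chi-square/Fisher on one prespecified per-patient binary outcome built on the stated cut-offs, for example all four ratings within 2–4 against any rating outside. This also gives score 1 a place.
3. **Single time points.** Show both scores by time point descriptively, without P values. For Ramsay, give the counts of 1 and of 5–6 separately so that direction is not lost.

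The cost is a few words and no new data. The change should be dated and fixed while the biostatisticians are still blinded to group. The main downside is the dilution noted in item 1.
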